### Statistical analysis

All analyses will be conducted on the intention-to-treat and per-protocol principles. Regardless of whether participants received the randomized treatment, the intention-to-treat principle considers all of them as randomized. A complete case analysis will be performed if missing data for the randomized participants accounts for less than 5% of total data. Multiple imputations will be used if missing data is more than 5%. Dropouts will be included in the analysis by multiple imputations for missing data. The effect that the per-protocol participants and missing data might have on results will be assessed via sensitivity analysis. Subgroup analysis will be performed based on age and gestational age.

The primary comparison, both doses vs. placebo, will be analyzed using a superiority analysis. We will use the *t* test for the continuous outcome. Meanwhile, high dose vs. placebo and low dose vs. placebo will also be analyzed using the *t* test. Other outcomes will be analyzed using noninferiority analysis. The mean (and standard deviation) will be expressed for continuous variables, and numbers (percentages) will be expressed for categorical variables. Group variances will be compared using Leven’s test at the 0.05 significance level. Analysis of variance (ANOVA) will be used to analyze continuous data, and the *chi*-square test or Fisher’s exact test will be used for categorical data. To investigate the effects of treatment and time course, repeated measures ANOVA will be applied to determine changes in the continuous outcome data at each visit. R 3.1 software will be used for analysis.

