Through their migratory, anti-inflammatory, and trophic properties, MSCs exert numerous functions that may be of relevance for restoring skin tissue function and enhancing healing [26]. Using a rabbit model, researchers found that human MSCs can regulate inflammation and prevent the formation of hypertrophic scars [27]. Previous results of clinical trials also demonstrated the benefits derived by the employment of MSCs in wound healing [28, 29]. Falanga *et al.* [30] indicated that MSCs can be safely and effectively delivered to wounds using a fibrin spray system. Another clinical trial showed that directly applied bone marrow-derived cells can lead to dermal rebuilding and closure of nonhealing chronic wounds [31]. Yoshikawa *et al.* [32] demonstrated that MSCs are therapeutically effective in patients with intractable dermatopathies. In addition, Dash *et al.* [33] showed that autologous implantation of bone marrow-derived MSCs in nonhealing ulcers accelerated the healing process and significantly improved clinical parameters.

In this trial, we hypothesize that MSCs can reduce hypertrophic scars and decrease wound infection after Cesarean delivery. Therefore, we undertake a Phase II clinical trial to evaluate the safety and efficacy of MSCs in the treatment of Cesarean section skin scars in a prospective, randomized, double-blind, placebo-controlled, single-center study.

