#### Secondary outcomes

The secondary outcome measures are as follows:The VSS at 1 and 3 months after treatmentThe VSS will be also evaluated at 1 and 3 months after treatment. The differences in the 1st and 3rd month will also be compared among the three groups.Wound healingWound healing status will be assessed 14 days after surgery using the REEDA scale. The REEDA scale contains five variables: redness, edema, ecchymosis, discharge, and the approximation of wound edges [19].Erythema and pigmentationThese will be measured using a narrowband reflectance spectrophotometer (Mexameter MX18) at 1, 3, and 6 months after treatment.Scar thickness and areaThe scar thickness and area will be measured using a high definition ultrasound device at 1, 3, and 6 months after treatment.Meanwhile, the mother’s milk will be collected at each visit and immunoglobulins (IgG, IgA, IgM) and complements (C3, C4) will be detected by the transmission immune turbidity method using an automatic biochemical analyzer.Participants’ satisfaction of the treatment will be measured using a satisfaction scale, including five categories, namely, none, slight, moderate, good, and very good.The number of hypertrophic scars and wound infections during the 6 months.Safety and tolerability of the intervention.

All adverse events, including side effects and other ailments, will be recorded in a case report form. The researcher will report all adverse events to the ethics committee. For all participants, additional services arising from all adverse events will be provided free of charge.

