Although previous results of trials with MSCs in wound healing have been reported, the application of MSCs on Cesarean section skin scars has not yet been investigated. In this prospective, randomized, double-blind, placebo-controlled study, we aim to investigate the possible effects of MSCs in women’s skin scars after Cesarean delivery. We hypothesize that MSCs can enhance wound healing, reduce hypertrophic skin scars, and decrease wound infection. To our knowledge, this trial is the first to investigate the potential of the therapeutic use of MSCs for the management of women’s skin scars after Cesarean delivery. The outcomes from this trial will help to determine the efficacy and safety of MSC treatment in Cesarean section skin scars. The results will also identify a therapeutically effective dose of MSCs in preventing hypertrophic scars and wound infections risk factors. It will give us an effective therapeutic strategy to combat Cesarean section skin scars, even with uterine scarring.

A limitation of this trial is that this is a single-center clinical trial, which will limit the extrapolation of results. Meanwhile, loss of participants at follow-up is possible, especially for nonresponders in the prospective trial study. Notwithstanding its limitations, this trial will suggest whether MSC can be a safe and effective in the treatment of Cesarean section skin scars.

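### The noninferiority framework set for every outcome except the primary contradicts the trial's hypotheses of benefit and the difference tests it names for the secondary efficacy outcomes

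*Protocol article*

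**What the plan says.** The Statistical analysis section sets two frameworks. For the primary: "The primary comparison, both doses vs. placebo, will be analyzed using a superiority analysis". For everything else: "Other outcomes will be analyzed using noninferiority analysis". No outcome is exempted and no later step to superiority is described.

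The same paragraph then names the methods. ANOVA and the categorical tests "will be used to analyze continuous data, and the *chi*-square test or Fisher’s exact test will be used for categorical data", and "repeated measures ANOVA will be applied to determine changes in the continuous outcome data at each visit".

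The Secondary outcomes section shows what falls under the second sentence: VSS at 1 and 3 months (to be compared for differences among the three groups), REEDA wound healing at 14 days, erythema, pigmentation, scar thickness and area, milk immunoglobulins and complements, satisfaction, safety and tolerability, and "The number of hypertrophic scars and wound infections during the 6 months".

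The hypotheses are directional. Background: "we hypothesize that MSCs can reduce hypertrophic scars and decrease wound infection after Cesarean delivery". Discussion: "We hypothesize that MSCs can enhance wound healing, reduce hypertrophic skin scars, and decrease wound infection". The Interventions section gives placebo hydrogel as the only control.

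**The concern.** Noninferiority asks whether the new treatment is worse than the control by more than a margin. It is useful against an active control whose benefit is worth keeping. Against placebo, a positive answer says only that the cells are not much worse than the gel without cells. That is not the question in the Background or the Discussion, both of which expect a benefit on scars and infection.

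The named tests do not fit the framework either. ANOVA, repeated measures ANOVA, chi-square and Fisher's exact test all take zero difference as the null, and none tests a margin. An analyst who follows the paragraph has two incompatible instructions for each secondary efficacy outcome, and the choice between them could be made after the data are seen. The easy shortcut is to take p > 0.05 from a difference test as noninferiority, which is invalid and, with groups this small, likely to hide harm.

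**Working it through.** The article states no figure for a noninferiority analysis, so there is none to reproduce. The point follows from setting its statements side by side, and the calculations only show scale.

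**Statements compared, for the secondary efficacy outcomes**

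| Source | Question implied |
|---|---|
| Background and Discussion | Do cells reduce hypertrophic scars and infection and improve healing? (superiority) |
| Secondary outcomes, VSS at 1 and 3 months | Do the three groups differ? (difference) |
| Statistical analysis, named tests | Is the difference zero? (difference) |
| Statistical analysis, framework sentence | Are cells not worse by a margin? (noninferiority) |

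The last row conflicts with the other three.

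**Inputs.** 30 women per group, so 60 on cells (both doses) against 30 on placebo, and VSS standard deviation 1.68 (both Sample size); wound infection 3% to 20% (Background). The margins and true effects below are assumptions for illustration.

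**1. An inert product can pass.** For VSS, SE = 1.68 × √(1/60 + 1/30) = 1.68 × √0.05 = 0.376. With no true effect, the chance of declaring noninferiority at margin m is Φ(m/SE − 1.96):

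| Assumed margin (VSS points) | Chance an inert product passes |
|---|---|
| 0.5 | 26% |
| 0.75 | 51% |
| 1.0 | 76% |
| 1.5 | 98% |

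A two-sided 5% superiority test would wrongly claim benefit 2.5% of the time. The exact percentages depend on the margin. That passing does not demonstrate a reduction does not.

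**2. Precision for infection.** With the same true rate p in both groups, the 95% half-width for the risk difference is 1.96 × √(p(1 − p) × 0.05):

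- p = 3%: 1.96 × √(0.0291 × 0.05) = 7.5 points; (3 + 7.5)/3 = 3.5 times the placebo rate
- p = 10%: 1.96 × √(0.09 × 0.05) = 13.1 points; (10 + 13.1)/10 = 2.3 times
- p = 20%: 1.96 × √(0.16 × 0.05) = 17.5 points; (20 + 17.5)/20 = 1.9 times

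The 3% line is rough: 30 × 0.03 = 0.9 placebo events are expected, too few for a normal approximation.

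**3. Nonsignificance is not noninferiority.** Suppose cells truly doubled the infection rate (an assumed harm). Summing over all binomial outcomes for 60 against 30, Fisher's exact test at 5% two-sided would be nonsignificant 99%, 84% and 57% of the time at placebo rates of 3%, 10% and 20%.

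**The case against.** **Differences are tested after all.** The paragraph names difference tests, and the Secondary outcomes section plans a comparison of VSS differences. This stands. A reader might infer that the secondary hypotheses would never be tested, but the documents do not support that. What they show is a contradiction over framework.

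**The scope is narrower than all other outcomes.** This also stands. Directional hypotheses are stated for hypertrophic scars, wound infection and wound healing, not for satisfaction or safety. For adverse events and milk immunoglobulins, whether cells are unacceptably worse than placebo is a reasonable question, so the framework is not wrong for every outcome it covers. It is wrong for the efficacy outcomes, which the sentence does not exempt.

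**A margin may be set in the full protocol or SAP.** It may, and its absence from an article is no fault. But no margin turns noninferiority to placebo into a test of reduction. A noninferiority interval could also be read for superiority, but the article plans no such step.

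**The infection illustration assumes no true difference.** Correct. If infection were halved, the expected upper limit would be lower: from 10% to 5%, −5 + 1.96 × √(0.05 × 0.95/60 + 0.10 × 0.90/30) = about +7 points; from 20% to 10%, about +6. Nor may a reader infer that any attainable margin accepts at least a doubling: at 20% the ratio is 1.9.

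**Superiority gains little for infection.** Fisher's test has about 3%, 13% and 22% power for an assumed halving from 3%, 10% and 20%. That is a reason to label these results supportive and report intervals. It is not a reason to keep a framework that answers another question.

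**Conclusion.** The point holds for the secondary efficacy outcomes. The framework sentence contradicts the hypotheses in the Background and Discussion, the comparison of differences under Secondary outcomes, and the tests named in its own paragraph. This rests on the text alone, not on any missing margin. The primary superiority comparison is unaffected.

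The figures show scale only. They assume 60 against 30 women with complete data; the infection intervals and the inert-product calculation also assume no true difference, and the latter uses assumed margins. That nonsignificant results would in fact be reported as noninferiority is a risk the wording leaves open; the article does not say it will happen.

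**What to change.** Delete the framework sentence from the Statistical analysis section. In its place state that:

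- Secondary efficacy outcomes (VSS at 1 and 3 months, REEDA, erythema, pigmentation, scar thickness and area, hypertrophic scars, wound infections) are compared for superiority with two-sided tests, effect estimates and 95% confidence intervals, as supportive results.
- Adverse events and milk immunoglobulins are reported as estimates with 95% confidence intervals.
- A nonsignificant difference test is not read as noninferiority for any outcome.

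The cost is wording only: the sample size, data collection and primary analysis are unchanged. The change should be made and dated before unblinding, so that the framework is not chosen with the results in view.

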### Sample size

Our sample size calculation is based on previous results from [name] preliminary trial in Taipei Medical University WanFang Hospital [42]. These results found that the mean VSS was 4.50 ± 1.68 in healthy pregnant women. The ratio of the MSC and control group sample size sets was 2:1. We will use the conventional values *α* = 0.05 and *β* = 0.1 for two-sided tests of probability. Meanwhile, we hypothesize that the difference in mean VSS at 6 months after treatment between the MSCs and placebo group will be *δ* = 1.5. The total sample size is estimated to be 74. Considering a dropout and other potential influencing factors, the final participant is estimated to be about 90 (*n* = 30 in each group).

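### The plan assigns the secondary outcomes, safety included, to noninferiority, but the tests it names are tests of no difference, which cannot show noninferiority or exclude harm

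*Protocol article*

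**What the plan says.** All references are to the protocol article.

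- **Aim (Background):** "we undertake a Phase II clinical trial to evaluate the safety and efficacy of MSCs in the treatment of Cesarean section skin scars".
- **Outcomes (Secondary outcomes):** the list includes the number of wound infections over 6 months and "Safety and tolerability of the intervention".
- **Analysis (Statistical analysis):** the primary comparison, both doses against placebo, is a superiority analysis by *t* test. All other outcomes are assigned to noninferiority. The same paragraph then allocates methods by data type: ANOVA for continuous data and, for categorical data, the chi-square "test or Fisher’s exact test will be used for categorical data". Numbers and percentages are promised for categorical variables.
- **Conclusion foreseen (Discussion):** "this trial will suggest whether MSC can be a safe and effective in the treatment of Cesarean section skin scars".

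**The concern.** A noninferiority analysis asks whether the data exclude an excess larger than some tolerable amount. It is answered by comparing a confidence limit with that amount, or by a test against a shifted null. Chi-square, Fisher's exact test and ANOVA ask whether the data are compatible with no difference at all. In a small trial a large *p*-value is easy to obtain, whatever the truth. The paragraph therefore states one objective and names tools built for another.

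For scar measures this is mainly a matter of clarity. For adverse events and wound infection more is at stake: donor-derived cells are applied to a freshly sutured incision, and the trial is meant to say something about safety. If the named tests are what the report relies on, a result that leaves a clinically important excess entirely possible would carry the label noninferiority.

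**Working it through.** **1. What the sample size was set for.** The Sample size section uses "We will use the conventional values *α* = 0.05 and *β* = 0.1 for two-sided tests of probability", an SD taken from "the mean VSS was 4.50 ± 1.68 in healthy pregnant women", a difference for which it says that the "placebo group will be *δ* = 1.5", and 2:1 allocation ("The ratio of the MSC and control group sample size sets was 2:1"). All of this concerns the Vancouver Scar Scale (VSS). The standard formula for the placebo group is

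n = (1 + 1/2) × [1.68 × (1.960 + 1.282) / 1.5]² = 1.5 × 3.631² ≈ 19.8, so 20 placebo + 40 MSC = 60.

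The stated 74 is not reproduced. That is a separate matter: it errs towards more women and does not affect this point. What matters here is that the final 90 (60 MSC, 30 placebo) was sized on VSS, and no event rate entered the calculation.

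**2. What a Fisher test can detect.** Inputs: 30 women per arm and no dropout. The only event rate in the article is wound infection, 3% to 20% (Background). Higher rates are assumptions, shown for range. Method: enumerate all pairs of counts from two independent binomials, add up the probability of the tables with two-sided Fisher *p* ≤ 0.05, and subtract from 1 to get the chance of missing a true doubling.

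| Placebo → MSC rate | Missed, 60 vs 30 (pooled) | Missed, 30 vs 30 (one dose) |
|---|---|---|
| 3% → 6% | 99% | over 99% |
| 10% → 20% | 84% | 90% |
| 20% → 40% | 57% | 70% |
| 25% → 50% | 40% | 59% |
| 30% → 60% | 24% | 44% |

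The chi-square test without continuity correction does not change the picture. Its pooled power over the 3% to 20% range is 2% to 48%.

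**3. What one such result would look like.** Take 3 of 30 events on placebo (10%) and 12 of 60 on MSC (20%).

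- Pooled rate 15/90 = 0.167. Null standard error √[0.167 × 0.833 × (1/30 + 1/60)] = 0.083. z = 0.10/0.083 = 1.2, so chi-square = 1.44 and *p* = 0.23.
- Unpooled standard error √(0.1 × 0.9/30 + 0.2 × 0.8/60) = 0.075. Approximate 95% CI for the risk difference: 0.10 ± 1.96 × 0.075, that is −4.8 to +24.8 percentage points.

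The named test reports no significant difference. The interval shows that an excess of more than 20 points is not excluded.

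**4. What intervals can deliver at this size.** If the observed rates are equal, the upper 95% limit for the risk difference (60 vs 30) is about 1.96 × √[p(1−p)(1/30 + 1/60)]: 7.5 points at 3%, 13.1 at 10% and 17.5 at 20%. With no events at all, the one-sided 95% upper bound is 1 − 0.05^(1/n): 4.9% for 60 women and 9.5% for 30.

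**The case against.** The strongest reply is that noninferiority is the stated framework for the secondary outcomes, that the chi-square and Fisher sentence is a generic line by data type which names neither adverse events nor safety, and that a margin may well be in the full protocol or analysis plan, which are not shown. Part of this stands. The absence of a margin from a journal article is not held against the plan. What remains is in print: the only methods named for these outcomes do not perform the analysis announced for them.

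A reader might infer that the trial will declare the gel safe whenever *p* exceeds 0.05. The article does not support that. It states no such rule, and the Discussion is hedged, saying only that the trial will suggest an answer. A reader might also treat safety as a co-equal aim. It appears beside efficacy in the Background, but VSS at 6 months is the primary aim and safety is the last item among the secondary outcomes. Nor does the article call the milk immunoglobulins a safety measure, so nothing here depends on them.

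It is also fair that a doubling is not always missed. Pooled power passes 50% at a placebo rate of about 25%, and an any-adverse-event composite could be that common. Wound infection, moreover, is an outcome the investigators expect to fall. An interval for the risk difference serves either direction.

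Finally, adverse events are reported to the ethics committee, and an independent committee reviews accumulating data. These protect participants during the trial but do not determine what the final analysis can conclude.

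**Conclusion.** The point holds as a mismatch between the stated objective and the named methods. Difference tests cannot deliver the noninferiority conclusion assigned to the secondary outcomes. For wound infection within the article's own range of rates, they would miss a true doubling more often than not, for pooled MSC as well as for a single dose. This rests on full follow-up of 30 women per arm; dropout would make it somewhat worse. For adverse events no base rate is given, so the size depends on how common the event is: the information is poor for uncommon events and fair for a composite affecting 25% to 30% or more of the placebo group. The finding is not that the trial is too small, since limited power for adverse events is normal for 90 women. It is that the printed analysis does not show the reader that limit.

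**What to change.** In the Statistical analysis section:

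- Reconcile the noninferiority sentence with the tests that follow. Either say which outcomes are to be tested for noninferiority, by confidence limits against a margin, or drop the term where only a comparison is meant.
- For adverse events and wound infection, report counts and percentages with exact (Clopper-Pearson) 95% CIs for each arm and for pooled MSC. Add a 95% CI (for example Miettinen-Nurminen) for the risk difference of each dose and of pooled MSC against placebo.
- State that a non-significant difference is not evidence of safety or of noninferiority.

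In the Discussion, describe the safety conclusion as preliminary and limited to what the upper confidence limit excludes. For instance, no events of a given kind in 60 treated women would leave true rates up to about 4.9% possible (one-sided 95% bound).

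The cost is a few sentences, with no additional women, visits or data. The downside is a more limited safety claim.

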### Data collection and management

All research investigators will be trained uniformly in standard operating procedures. A regular monitoring scheme will be set up to collect accurate and valid data. Non-numeric data will be converted into numbers for storage. All laboratory specimens will be identified only by a coded identification number to maintain participant confidentiality. To ensure confidentiality, data dispersed to project team members will be blinded to any identifying participant information. After verification of the content, two research investigators will independently input the data into a database. All participant information will be kept safely under confidential conditions and archived for 10 years. The project principal investigator could access the full data. Participant recruitment is currently in progress. The first participant was recruited on 14 September 2016.

Meanwhile, a data monitoring committee will be established, which will be independent of the study organizers and will periodically review the accumulating data and determine whether the trial should be modified or discontinued. The committee members will perform independent review of trial processes every 2 months.

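### Satisfaction is a five-level ordered outcome, but the test stated for categorical data (chi-square or Fisher's exact) ignores the order and gives up power

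*Protocol article*

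**What the plan says.** The Secondary outcomes section says that participants' satisfaction is "measured using a satisfaction scale, including five categories, namely, none, slight, moderate, good, and very good". Table 2 schedules it at weeks 4, 12 and 24.

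The Statistical analysis section sorts variables into two classes:

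- For continuous variables, "Analysis of variance (ANOVA) will be used to analyze continuous data", with t tests for the dose-versus-placebo comparisons of the primary outcome.
- For categorical variables, "numbers (percentages) will be expressed for categorical variables", and the test is chi-square or Fisher's "exact test will be used for categorical data".

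The article names no rank test, trend test or ordinal model. The same section also states: "Other outcomes will be analyzed using noninferiority analysis".

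The section on data collection says "Non-numeric data will be converted into numbers for storage". That concerns the database and does not choose an analysis.

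**The concern.** The satisfaction levels have a natural order, and a useful treatment would be expected to move women up the scale. Pearson chi-square and Fisher's exact test give the same answer if the five labels are shuffled. They treat a step between the two lowest levels like a jump from the lowest to the highest. On the three-arm table chi-square spreads its sensitivity over (3 − 1) × (5 − 1) = 8 degrees of freedom, most of which have nothing to do with an upward shift.

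At stake is the sensitivity of the one outcome listed that records the women's own view of the treatment, in a trial with 30 women per arm. The Background names dissatisfaction after Cesarean delivery as part of the motivation. This is a question of efficiency. It does not put the type I error in doubt.

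**Working it through.** **Inputs from the article.** Five ordered categories (Secondary outcomes). Thirty women per arm and a two-sided 0.05 level (Sample size; the level is stated there for the VSS). The article gives no effect, distribution or power for satisfaction, so there is no figure of its own to reproduce. Its total of 74 concerns the VSS and is not used here.

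**Assumptions, not in the article.** Placebo distribution 5/15/35/30/15% from lowest to highest, and the same proportional-odds shift in both dose groups.

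**Formula for the shift.** For each cut point j, the treated odds of being at or below j are the placebo odds divided by the odds ratio (OR): F_T = (o/OR)/(1 + o/OR), with o = F_P/(1 − F_P). At OR 2.5:

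- F_P = 0.05: o = 0.0526, o/OR = 0.0211, F_T = 0.021
- F_P = 0.20: o = 0.25, o/OR = 0.10, F_T = 0.091
- F_P = 0.55: o = 1.222, o/OR = 0.489, F_T = 0.328
- F_P = 0.85: o = 5.667, o/OR = 2.267, F_T = 0.694

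The treated distribution is therefore about 2/7/24/37/31% (rounded).

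**Tests, compared like for like.** Three groups: Pearson chi-square (8 df) against Kruskal-Wallis (2 df). Pooled doses (60) against placebo (30): chi-square (4 df) against Wilcoxon (1 df). Loss = 1 − power(chi-square)/power(rank test).

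**Simulated power, 4,000 trials per setting, placebo 5/15/35/30/15%:**

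| OR | Comparison | Chi-square | Rank test | Loss |
|---|---|---|---|---|
| 2.5 | three groups | 27% | 49% | 1 − 27/49 = 45% |
| 2.5 | pooled | 41% | 61% | 1 − 41/61 = 33% |
| 3 | three groups | 40% | 66% | 1 − 40/66 = 39% |
| 3 | pooled | 57% | 76% | 1 − 57/76 = 25% |

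A separate run gave 28% against 49% and 41% against 59% at OR 2.5, and 39% against 64% and 57% against 77% at OR 3. With no effect, all tests rejected in 4.4% to 5.6% of trials.

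**Smaller and larger effects (placebo 10/20/40/20/10%, equal doses, 30 per arm).** At OR 2, 15% against 30% (three groups) and 23% against 38% (pooled), losses of about 50% and 40%. At OR 5, 76% against 94% and 90% against 97%, losses of about 19% and 7%. A check at OR 2 with the 5/15/35/30/15% distribution falls within the ranges given in the conclusion.

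**Other assumptions.** Four placebo shapes were tried (symmetric, uniform, skewed high, skewed low), with the effect graded by dose in the three-group comparison. Chi-square kept 51-56% of Kruskal-Wallis power there at OR 2-3, and 54-76% of Wilcoxon power in the pooled comparison. With 25 women per arm (placebo 10/20/40/20/10%, equal doses), OR 3 gave 31% against 58% (three groups) and 47% against 69% (pooled).

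**Analytic check.** Give both tests the same noncentrality. Where a 1-df test has 80% power (noncentrality 7.85), a 4-df chi-square has 60%. Where a 2-df test has 80% (9.63), an 8-df chi-square has 57%. The losses are 1 − 60/80 = 25% and 1 − 57/80 = 29%, in line with the pattern that losses shrink as power rises.

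**The case against.** **The assignment is inferred.** The Statistical analysis section does not mention satisfaction. The outcome is called a scale, its levels will be stored as numbers, and the VSS, itself a score built from graded items, is analysed by t test. An ANOVA on scores of 1 to 5 is therefore possible. This stands as a caveat. Even so, the article describes the outcome by its categories, which makes the categorical rule the more natural reading.

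**An article leaves such detail to the SAP.** That would answer a complaint that something is missing. Here the article states a rule for categorical data without exception, and the rule suits this outcome poorly.

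**Chi-square is valid, and the simulated shift favours rank tests.** Both are true. The gain depends on the effect being a shift along the scale, which is the effect one would hope to detect on such a scale.

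**Stronger readings that the documents do not support:**

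- A reader might infer that power is roughly halved in general. Setting the three-group chi-square (27% at OR 2.5) beside the pooled Wilcoxon (61%) gives that impression, but those tests address different comparisons. Like for like, a loss near half appears in the three-group table, or with one dose against placebo, when effects are small.
- A reader might infer that a real shift would usually be missed. Pooled chi-square detects OR 3 in 57% of simulated trials, and at OR 2.5 Kruskal-Wallis itself reaches only 49%.
- A reader might infer that a significant result would leave the direction unknown. The plan reports percentages by category, so the direction could be seen. Kruskal-Wallis gives no direction either.

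**Two limits remain.** Fisher's exact test was not simulated, although it may well be used: the lowest placebo category would hold 0.05 × 30 = 1.5 women on average. It ignores order as well, but the figures apply to Pearson chi-square only. Also, the sentence that puts the other outcomes under noninferiority sits badly with any plain test of difference, and replacing chi-square by Wilcoxon does not settle that.

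**Conclusion.** The point holds as a modest improvement. On the natural reading, an ordered five-level outcome is tested by methods that are valid but discard the order. With 30 per arm, a placebo distribution of 5/15/35/30/15% and a proportional-odds shift of OR 2 to 3, chi-square loses about 40-50% of Kruskal-Wallis power across three groups and about 25-40% of Wilcoxon power for pooled doses against placebo. Across other placebo shapes the pooled loss runs from 24% to 46% (power kept 76% to 54%), and at OR 5 losses are clearly smaller. The distribution and the odds ratios are assumptions, because the article gives neither. Satisfaction is a secondary outcome on which the trial was not sized, and no conclusion on the primary VSS outcome depends on it.

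**What to change.** Add to the Statistical analysis section: satisfaction will be analysed by a proportional-odds model giving an odds ratio with 95% CI, for pooled doses against placebo and then for each dose against placebo. A Wilcoxon rank-sum test for the same comparisons is the simpler alternative. Restrict chi-square and Fisher's exact test to nominal or binary outcomes such as wound infection. Counts and percentages by category should still be reported.

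The same sentence should say whether satisfaction is tested for a difference or for noninferiority. The model's odds ratio and interval give a directional estimate that can be used either way, whereas an unordered chi-square cannot support a noninferiority conclusion.

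The cost is a small change of wording, with no new data or visits. The model adds a proportional-odds assumption. The primary VSS analysis stays as it is.
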